### 2.2. Eligibility Criteria

Subjects aged 3 to 12 years diagnosed with PFF. For the diagnosis of the PFF, the following criteria must be met:Foot Posture Index (FPI) > 6 [33].Navicular drop > 10 mm [34].Relaxed calcaneal stance position (RCSP) 6° to 12° valgus [35].Pronation angle > 10° [36].Arch index > a 1.35 [37].Double/single heel rise test negative [38].Windlass test negative [39].

In addition, the signature of the parents or legal guardians with consent to participate in the study will be necessary (Appendix B).

Participants will be excluded if they have undergone any surgery in the lower limbs, have previously received treatment for PFF, present osteoarticular injury, foot fractures or in the lower limbs in the last 6 months, ankle sprain, asymmetry, systemic diseases with osteoarticular involvement that present symptoms in the lower limb with gait disturbance (for example, Perthes disease) or biomechanical alteration of the lower limb with repercussions on the foot and ankle. Children suffering from any type of neurological or systemic disability (cerebral palsy, Down Syndrome, clubfoot or equino-varus, …) will also be excluded.

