
#### 2.4.2. Quantitative or Numerical Variables

Age: in months.Weight: in Kg.Height: in meters.Body Mass Index (BMI): Will be calculated with the formula weight (Kg) divided by height squared (meters^2^). The classification of each child in low weight, normal weight, overweight or obesity will depend on the child’s sex, height, weight and age [44].Pain: visual analog scale (from 1 to 10, 1 being minimum pain and 10 maximum pain).FPI: The six clinical criteria used in PFI are: 1. palpation of the talus head; 2. curvature supra and lateral inframaleolar region; 3. position of the calcaneus in the frontal plane; 4. prominence of the talonavicular region; 5. congruence of the internal longitudinal arch and 6. abduction/adduction of the forefoot with respect to the rearfoot. (Score: neutral = 0; clear signs of supination = −2; clear signs of pronation = +2) [33].RCSP: degrees of calcaneal eversion. The valgus degrees of the calcaneus are measured in bipedal support [35].Navicular drop: in millimeters. It measures the difference between the navicular position when the patient’s foot is in a neutral position and when the patient’s foot is in its normal position. It measures how many millimeters the medial tuberosity of the scaphoid has descended [34].Pronation angle: in degrees. To calculate the bisection of the distal third of the tibia with respect to the bisection of the calcaneus [36].Chippaux-Smirak index: in cm. On the footprint of the subject taken from a pedigraphy, the narrowest distance from the medial part of the foot (B) with the widest distance from the forefoot (A) must be measured. It is divided B/A [45].Pressure platform: percentage of load/weight on each foot and distribution of the same (anterior load, posterior load, load of the left and right foot) [43].Arch index: numerical scale. The patient’s footprint is taken with a pedigraphy, the toe area is excluded and a longitudinal line is drawn that goes from the center of the heel to the 2nd toe. A line is then drawn perpendicular to the 1st. Two lines are drawn perpendicular to this axis to see the anterior extent of the forefoot area. The axis of the foot is divided into 3 equal parts and here 3 zones are defined: A: forefoot, B: midfoot and C: rearfoot. The arch index is calculated: B/(A + B + C) [37].Foot size: in cm.Silfverskiold test: in degrees. The degrees of dorsiflexion of the ankle (starting from a position of 90°) with extended knee and bent knee [46] will be measured.Navicular height: in millimeters. Measure the height of the scaphoid to the ground with the subject sitting [47].

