## Appendix C. Patient Medical History and Report

**Table A2 jpm-13-01269-t0A2:** Patient Medical History and Report.

ANAMNESIS.		
Name:		Identification Code:
Name and ID father/mother/legal guardian:		
Address:		Phone:
DNI:	Email:	
Date of birth:		Age:
Weight:	Height:	BMI:
Allergies:	Background:	
Standing number:	Gender: Male/Female	
Level of physical activity:	High/Medium/Low	
Exploration-Assessment		
IPF	Punctuation:	Pronated/Normal/Supinate
Navicular Drop	(mm)	
Double Heel Rise Test	Positive/Negative	
Single Heel Rise Test	Positive/Negative	
Pain (VAS scale)	Symptomatic/Asymptomatic	Punctuation:
PRCA	(degrees)	
Windlass Test	Positive/Negative	
Arc height index	Punctuation:	
Maximum pronation test	Positive/Negative	
ASA axis	Lateralized/Neutral/Medialized	
Supination resistance test	High/Moderate/Low	
Chippaux-Smirak Index	(cm)	
Beighton scale	Punctuation:	Hyperlax/Normal
Type of forefoot	Abduccido/Neutral/Adducido	
Footwear	Heel level: Medial/Center/Lateral	
Podoscope	Pronate/Supine/Neutral	
Pronation Angle	(degrees)	
Silfverskiold Test	(degrees)	
Navicular height	(mm)	
Pressure platform		
Maximum pressure zone:		
Center of gravity		
Gait progression line		
Load/weight percentage	Left	Right
	Ant: Post:	Ant: Post:
	Left:	Dx:

**
REPORT EXERCISES AND RECOMMENDATIONS
**

Exercises to be performed:

1. Tiptoe for 1 min.
2. Walk with the outer lateral edge of the foot for 1 min.
3. Stand on tiptoe, hold on for 2 s and go down 15 times.
4. Hold a tennis ball with your heels and stand on tiptoe without the ball falling, hold 2 s and go down. Perform 15 repetitions.
5. Take marbles or pens with your toes and try to put them in a bucket or change them for 1 min.
6. Stand on a towel or paper and crumple it with your toes, make this gesture for a minute.
7. Standing try to increase the arch of the foot making the greatest possible effort, do 15 repetitions.
8. To finish, standing with a ball under the sole of the foot make pressures at different points of the foot and perform stretching of the triceps sural with extended knee and bent knee.

All exercises will be repeated twice each.

All these exercises will not structure the deformity and do not develop compensations in other body segments. With them we are working all the intrinsic and extrinsic muscles of the foot involved in children’s flatfoot. The rebalancing of this musculature will cause the stabilizing function of the foot to develop, in addition to improving its correct activation during dynamics.

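### The arch-index entry criterion (above 1.35) cannot be met on the index as the protocol defines it, which runs from 0 to 1

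*Protocol article*

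**What the plan says.** Three places in the protocol article bear on this measure.

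- **Section 2.2 (Eligibility Criteria)** introduces its list with "For the diagnosis of the PFF, the following criteria must be met". One item is "Arch index > a 1.35 [37". The section gives no rule under which only some of the items need be satisfied.
- **Section 2.4.2 (Quantitative or Numerical Variables)** describes how the index is obtained: "The patient’s footprint is taken with a pedigraphy, the toe area is excluded", the long axis of the foot is cut into three equal parts, and "3 zones are defined: A: forefoot, B: midfoot and C: rearfoot". It then states: "The arch index is calculated: B/(A + B + C) [37". The reference number is the one attached to the entry cut-off.
- **Appendix C**, which Section 2.4 presents as the form holding all the variables to be studied, has no line labelled as the arch index. Its nearest entry is "Arc height index", recorded as a score, with no formula.

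**The concern.** The cut-off and the formula carry the same name and the same reference, yet they cannot describe the same quantity. The numerator of the ratio is one of the three terms of its own denominator, so the ratio cannot pass 1, while the entry rule demands more than 1.35.

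What is at stake is the case definition. The criterion is one of a mandatory list, so an assessor who applies the text as written must turn every child away. An assessor who enrols a child has dropped the criterion, used another cut-off or used another ratio, and the article does not say which. A reader of the results could not reconstruct who was eligible. This matters more than usual here, because Section 1 makes defining pediatric flat foot a specific objective, and Section 3 says the definition will come from the common findings in the sample. The entry criteria decide in part what those findings are.

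**Working it through.** **Inputs**

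- Cut-off: arch index AI > 1.35 (Section 2.2).
- Formula: AI = B/(A + B + C) (Section 2.4.2).
- A, B and C are zones of one footprint without the toes (Section 2.4.2). Each is therefore zero or positive, and their sum is positive.
- Target enrolment: 168 (Section 2.6).

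**Range of the index.** Since A + C ≥ 0, B ≤ A + B + C. Hence 0 ≤ AI ≤ 1, and AI = 1 only if the whole footprint is midfoot.

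**Can the cut-off be reached?**

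1. B/(A + B + C) > 1.35
2. B > 1.35A + 1.35B + 1.35C
3. B(1 − 1.35) > 1.35(A + C)
4. −0.35B > 1.35(A + C)

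The left side is zero or negative and the right side is zero or positive, so there is no solution. The gap between the cut-off and the maximum is 1.35 − 1.00 = 0.35. The argument does not depend on whether the zones are measured as areas or as any other non-negative quantity.

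**Numerical check.** In 1,000,000 random non-negative triples, weighted heavily towards the midfoot, the largest index was 0.99999 and none exceeded 1.35.

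**Would a percentage scale rescue it?** Section 2.4.2 calls the index a numerical scale and gives no factor of 100. If 1.35 were nevertheless read as 1.35%, the criterion would be AI > 0.0135, which is B > (0.0135/0.9865)(A + C) = 0.0137(A + C). A midfoot print of about 1.4% of the rest of the footprint would pass. Such a rule would admit feet with almost no midfoot contact, so it could not serve to identify a collapsed arch.

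**Would another ratio in the article rescue it?** The only other footprint ratio in Section 2.4.2 is the Chippaux-Smirak index, B/A, where the letters stand for widths. It has its own name and its own reference and no entry cut-off. Nothing in the article moves the 1.35 to it.

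**The case against.** The best case on the other side is that this is a slip and not a design fault. The criterion contains a stray letter before the number, which fits an editing or translation error. The limits for navicular drop, calcaneal stance position and pronation angle are still stated, so the case definition does not rest on the arch index alone. Allocation is random, so an unclear entry cut-off harms the description and reproducibility of the population more than the comparison between groups.

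All of that is fair. It does not remove the contradiction, because the article does not show which half is the slip, and no reader can correct it safely without the cited source.

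A reader might also infer four stronger things, which the documents do not support:

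- **That the trial will recruit nobody.** The 0% is a property of the literal wording. The likelier event is that staff apply some unstated working rule.
- **That the form records a different, third measure, so the arch index goes unrecorded.** Appendix C gives no formula. The form is loosely translated elsewhere too (IPF where the text has FPI, for example), so its entry may be the arch index under another label. It adds doubt and proves nothing more.
- **That each university site will devise its own cut-off.** Section 2.1 names two universities and nearby schools as sources of patients. It does not say that they assess eligibility separately.
- **That the outcome data are spoiled.** The impossible number is the entry cut-off, and Section 2.7 makes no use of it. The arch index as a study variable is affected only if the formula in Section 2.4.2 is the wrong half.

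**Conclusion.** The point holds and needs correction. As written, a mandatory entry criterion lies 0.35 above the highest value that its own index can take, so no child can meet it. This rests on two readings only: that the listed criteria are all required, as "the following criteria must be met" says, and that the three zones cannot be negative. It needs no outside source.

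The practical size is smaller than that 0% suggests but still material: one of the listed diagnostic criteria has no usable threshold, and the written rule does not define the population to be enrolled. Whether the measured variable is also wrong depends on which of the two statements is in error, and the article leaves that open.

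**What to change.** Check Section 2.2, Section 2.4.2 and Appendix C against the cited source and make them agree on one index, with one formula and a cut-off attainable on that index's scale. There are two routes:

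- If the formula is right, replace the cut-off with the one that the source gives for that ratio.
- If the cut-off is right, replace the formula in Section 2.4.2 with the ratio to which the cut-off belongs.

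This review does not propose a value. In either case, give the form field the same name as the index.

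The cost is one criterion, one definition and one form label in a short amendment. Appendix A places recruitment in August 2023 and the start of data collection in September 2023, so it cannot be assumed that the change precedes enrolment. If children have already been enrolled, document which index and cut-off were actually applied to them and report this with the results.

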### 2.3. Interventions

At the first visit, parents will be informed of their child’s current problem, treatments, and the existence of this study. In the case of accepting to participate in the study, the process will begin: all the variables will be carefully collected, the treatment will be established and an appointment will be made for follow-up at 6 months.

First, all the affiliation data will be collected and the PFF will be diagnosed.

#### 2.3.1. Group 1

For custom insoles, a mold will be taken using phenolic foam. To do this, the child will be asked to sit in a chair (to take the mold semi-load baring). The mold will be taken in a corrected position, that is, limiting the internal rotation of the tibia with one hand and the windlass mechanism will be performed to increase the MLA. The mold must remain neutral, so in the event that a varus or valgus print has emerged, this process will be repeated. Once we have the mold filled with plaster, two modifications will be made: a moderate medial heel skive (5 mm and an angulation of 15°) in the hindfoot and a slight inversion balance of 4° in the forefoot. Once the mold is prepared, the FO will be thermoformed; for this, we will use a 3 mm polypropylene, 25 Shore-A EVA as lining and 65 Shore-A EVA to stabilize the hindfoot.

In addition, the exercises to be performed will be explained to them and they will be given all the recommendations regarding the performance of exercises, the use of FOs and shoe therapy. These explanations will be provided in an additional report (Appendix C) that will be given to all subjects together with a calendar so that they write down all the days they perform the exercises with an X.

The exercises will first be explained by the podiatrist to the child and the parent/legal guardian. In addition, a standard video will be created so that the child can see it, in which the exercises will be explained through drawings in order to capture the attention of the child. The parent/legal guardian needs to confirm that the child is doing it correctly.

Once the FO have been provided, after assessing that it adapts well to the foot and does not cause discomfort, the patient will be requested to come in at 6 months. In the event that there is any discomfort or irritation to the child’s skin, an appointment will be made to readjust or modify the FO (in this visit the variables will not be evaluated, only the FO will be fixed; if there are no problems, this visit will not be carried out).

#### 2.3.2. Group 2

The participants will have the same intervention described for group 1, with the difference that they will use a placebo FO. This will be constructed using flat 1 mm 65 shore Ethylene-vinyl acetate (EVA), which will be cut to the foot size of the child and covered with the same top cover as the FO Group 1 to visually prevent them from being distinguished.

The instruments necessary for the development of this study and the budget necessary to carry out this clinical trial are included in Appendix D.

### 2.4. Outcomes Measures

The document presented in Appendix C will be used for data collection. It contains all the data to be collected in the anamnesis and all the variables to be studied, including all the clinical tests that would be carried out.

#### 2.4.1. Qualitative or Categorical Variables:

Gender: masculine or feminine.Pain: symptomatic or asymptomatic.Level of physical activity: high-low-nil.Double/simple heel rise test: Standing on toes with two legs/one leg for 25 repetitions. It will be considered positive if the participant is incapable due to fatigue or if when raising the calcaneus does not present a varus position [38].Supination resistance test: high-moderate-low. The patient is instructed to stand relaxed without any attempt to move the foot or lift the arch. The examiner’s fingertips are then placed plantar to the medial half of the navicular, and the examiner exerts a significant lifting force on the navicular. A normal foot will demonstrate subtalar joint supination with minimal lifting force. A pes valgus deformity will need extreme amounts of lifting force in order to produce little, if any, subtalar joint supination motion [40].Subtalar joint axis: Lateralized-neutral-medialized. The center of the neck of the talus should be located and marked to see the lateralized or medialized point, or if, on the contrary, it stops at the 2nd finger, which would indicate that it is neutral [36].Shoe wear at heel level: medial-center-lateral.Maximum pronation test: Positive or negative. The patient is asked to try pronate as much as possible; it is considered positive when performing the maneuver, the calcaneus cannot pronate more than 2° [41].Forefoot: adduction-neutral-abduction position [36].Foot posture index (FPI): Normal = 0 to +5; pronated = +6 to +9; highly Pronated = +10 to +12; supinated = −1 to −4 and highly supinated = −5 to −12. The six clinical criteria assessed: 1. palpation of the talus head; 2. lateral supra and inframalleolar curvature; 3. position of the calcaneus in the frontal plane; 4. prominence of the talonavicular region; 5. congruence of the internal longitudinal arch and 6. abduction/adduction of the forefoot with respect to the rearfoot. As we observe them, the following score is given: neutral = 0; clear signs of supination = −2; clear signs of pronation = +2 [33].Test of windlass: Positive or negative. It will be considered positive if, when performing dorsiflexion of the hallux, there is not supination of the foot, plantarflexion of the 1st ray, increase in the MLA and internal rotation of the tibia [39].Beighton scale: Hypermobility or normal. Subjects are rated on a 9-point scale, considering 1 point for each hypermobile site. These 9 points are: 1-hyperextension of the elbows (more than 10°), 2-passively touch the forearm with the thumb, having the wrist in flexion, 3-passive extension of the index finger to more than 90°, with the palm of the hand resting on the bed, 4-hyperextension of the knees (10° or more), patient in supine position and 5-flexion of the trunk forward touching the ground with the palms of the hands by bending without bending your knees. To be considered as hypermobile, it is required to have 4 points or more of the total of 9 [42].Podoscope: pronated-supinated-neutral [36].Pressure platform: maximum pressure zone, location of the center of gravity, gait progression line [43].

#### 2.4.2. Quantitative or Numerical Variables

Age: in months.Weight: in Kg.Height: in meters.Body Mass Index (BMI): Will be calculated with the formula weight (Kg) divided by height squared (meters^2^). The classification of each child in low weight, normal weight, overweight or obesity will depend on the child’s sex, height, weight and age [44].Pain: visual analog scale (from 1 to 10, 1 being minimum pain and 10 maximum pain).FPI: The six clinical criteria used in PFI are: 1. palpation of the talus head; 2. curvature supra and lateral inframaleolar region; 3. position of the calcaneus in the frontal plane; 4. prominence of the talonavicular region; 5. congruence of the internal longitudinal arch and 6. abduction/adduction of the forefoot with respect to the rearfoot. (Score: neutral = 0; clear signs of supination = −2; clear signs of pronation = +2) [33].RCSP: degrees of calcaneal eversion. The valgus degrees of the calcaneus are measured in bipedal support [35].Navicular drop: in millimeters. It measures the difference between the navicular position when the patient’s foot is in a neutral position and when the patient’s foot is in its normal position. It measures how many millimeters the medial tuberosity of the scaphoid has descended [34].Pronation angle: in degrees. To calculate the bisection of the distal third of the tibia with respect to the bisection of the calcaneus [36].Chippaux-Smirak index: in cm. On the footprint of the subject taken from a pedigraphy, the narrowest distance from the medial part of the foot (B) with the widest distance from the forefoot (A) must be measured. It is divided B/A [45].Pressure platform: percentage of load/weight on each foot and distribution of the same (anterior load, posterior load, load of the left and right foot) [43].Arch index: numerical scale. The patient’s footprint is taken with a pedigraphy, the toe area is excluded and a longitudinal line is drawn that goes from the center of the heel to the 2nd toe. A line is then drawn perpendicular to the 1st. Two lines are drawn perpendicular to this axis to see the anterior extent of the forefoot area. The axis of the foot is divided into 3 equal parts and here 3 zones are defined: A: forefoot, B: midfoot and C: rearfoot. The arch index is calculated: B/(A + B + C) [37].Foot size: in cm.Silfverskiold test: in degrees. The degrees of dorsiflexion of the ankle (starting from a position of 90°) with extended knee and bent knee [46] will be measured.Navicular height: in millimeters. Measure the height of the scaphoid to the ground with the subject sitting [47].

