## Abstract

Pediatric flat foot (PFF) is a very frequent entity and a common concern for parents and health professionals. There is no established definition, diagnostic method, or clear treatment approach. There are multiple conservative and surgical treatments, the implantation of foot orthoses (FO) being the most used treatment. The evidence supporting FO is very thin. It is not clearly known what the effect of these is, nor when it is convenient to recommend them. The main objective of this protocol is to design a randomized controlled trial to determine if personalized FO, together with a specific exercise regimen, produce the same or better results regarding the signs and symptoms of PFF, compared to only specific exercises. In order to respond to the stated objectives, we have proposed a randomized controlled clinical trial, in which we intend to evaluate the efficacy of FO together with strengthening exercises, compared to a control group in which placebos will be implanted as FO treatment along with the same exercises as the experimental group. For this, four measurements will be taken throughout 18 months (pre-treatment, two during treatment and finally another post-treatment measurement). The combination of FO plus exercise is expected to improve the signs and symptoms (if present) of PFF compared to exercise alone and the placebo FO group. In addition, it is expected that in both conditions the biomechanics of the foot will improve compared to the initial measurements.

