
### 2.5. Blinding and Monitoring

Participants and their parents/guardians will be blinded as to which group they are allocated to and will not see the other group.

An initial assessment will be made, these same measurements will be repeated 3 times throughout the duration of the study. In total we will obtain 4 measurements for statistical analysis.

The second measurement will be a month of treatment; in addition, in this visit we will assess the state of the FO and verify that the exercises are going well. We will ask about the FO, if any pain has appeared that was not there before, any blisters or reddened areas. In the event that the adaptation to the FO has not been good, we will make the necessary adjustments to the FO, such as lowering the MLA. If any subject needs their FO to be modified, they will be called by telephone after 2 weeks to see the evolution; in the event that it has not improved, it will be cited to re-evaluate the FO.

To corroborate that the execution of the exercises is good, we will ask the participant to repeat them, and in case there is an exercise that is not being performed correctly, we will explain it again.

The third assessment will be in the middle of the treatment/study period, that is, at 6 months. At this stage, all the initial measurements/assessments will be conducted again, as well as the last one at 12 months.

The estimated time for the measurement assessments is one hour for the 1st visit and 30 min for the rest of the visits.

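### The numeric pain score runs from 1 to 10 with no value for no pain, although pain-free children are eligible, and an unadjusted comparison of it carries avoidable spread

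*Protocol article*

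**What the plan says.** Section 2.4.2 of the protocol article defines the only numeric symptom score: "Pain: visual analog scale (from 1 to 10, 1 being minimum pain and 10 maximum pain". Section 2.4.1 adds a two-level item, "Pain: symptomatic or asymptomatic". The data collection form in Appendix C puts both on one row, with a blank for the score and no anchors.

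Pain is not an entry condition. Section 2.2 admits "Subjects aged 3 to 12 years diagnosed with PFF", and every diagnostic criterion listed there concerns foot posture or function. The abstract expects the intervention to "improve the signs and symptoms (if present) of PFF". At the one-month visit (2.5) the team asks "if any pain has appeared that was not there before". Section 2.5 also states that "these same measurements will be repeated 3 times throughout the duration of the study", so pain is recorded four times.

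Section 2.7 compares quantitative variables between groups by Student's t or ANOVA, or by rank tests if the data are not normal. It describes no allowance for pain at baseline. No outcome is named as primary, and 2.6 does not name the variable behind its sample size.

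**The concern.** The objective in the Introduction covers signs and symptoms, and the VAS is the only numeric measure of symptoms. A scale whose lowest value is labelled minimum pain leaves the pain-free state undefined. Assessors must choose between writing 1 and leaving the field empty, and neither 2.4.2 nor the form says which. Recruitment draws on two universities and on schools, so practice could differ.

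If pain-free children are scored 1, full relief and minimal residual pain look the same on the VAS. If they are left blank, a child whose pain resolves leaves the mean, and missingness then depends on the outcome.

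The second matter is precision. Pain-free children start at the floor of the scale and cannot improve on it. When their scores are pooled with those of symptomatic children and compared without adjustment, the distance between the two kinds of child enters the error variance.

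**Working it through.** **Step 1: the scale against the population.** Section 2.4.2 gives values from 1 to 10, with 1 as minimum pain. Sections 2.2, 2.4.1 and 2.5 and the abstract all allow for children without pain. A state the plan foresees at all four measurements therefore has no assigned number.

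**Step 2: the plan's own figures.** The article gives no mean, SD, effect or symptomatic share for pain, so there is no pain figure to reproduce. The only figure taken from it is the 64 children per group in 2.6, used here as a group size.

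**Step 3: illustration of the pooling loss.** Assumed: SD 2 among symptomatic children, a 1-point effect in them, a symptomatic control mean of 4, pain-free children scored 1 with no spread, final scores compared, two-sided 5% t-test, and symptomatic share *s* of 1, 0.5 or 0.3.

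- All children, unadjusted: difference = *s* × 1. Variance = 2²*s* + (4 − 1)²*s*(1 − *s*) = 4*s* + 9*s*(1 − *s*).
- Symptomatic children only: standardised effect *d* = 1/2 = 0.5, with 64*s* children per group.
- All children, adjusted for baseline symptomatic status: the between-type term drops out and the variance is 4*s*.

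| *s* | Unadjusted, all children | Symptomatic only | Adjusted, all children |
|---|---|---|---|
| 1 | variance 4; *d* = 0.5; power 80% | same | same |
| 0.5 | variance 2 + 2.25 = 4.25; *d* = 0.5/2.062 = 0.243; power 28% | 32 per group; power 50% | variance 2; *d* = 0.5/1.414 = 0.354; power 51% |
| 0.3 | variance 1.2 + 1.89 = 3.09; *d* = 0.3/1.758 = 0.171; power 16% | 19 per group; power 32% | variance 1.2; *d* = 0.3/1.095 = 0.274; power 34% |

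**Step 4: what causes the fall from 80%.** At *s* = 0.5, 80 − 50 = 30 points come from having fewer symptomatic children and 50 − 28 = 22 points from pooling. At *s* = 0.3 the split is 80 − 32 = 48 points and 32 − 16 = 16 points. Only the pooling part can be avoided by analysis.

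**Step 5: sensitivity to the variance model.** The formula gives both arms the control-arm variance. In the treated arm the symptomatic mean would be 3, so the between-type term there is (3 − 1)²*s*(1 − *s*) = 4*s*(1 − *s*).

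- At *s* = 0.5 the average variance is (4.25 + 3.00)/2 = 3.625, *d* = 0.263 and power is 31%.
- At *s* = 0.3 it is (3.09 + 2.04)/2 = 2.565, *d* = 0.187 and power is 18%.

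If pain is instead analysed as change from baseline, with SD 2 for change in symptomatic children and no change in pain-free children, power at *s* = 0.5 is about 49% (normal approximation). The pooling loss is thus a feature of unadjusted final scores.

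**The case against.** The strongest reply is that the form already separates the two states. The symptomatic/asymptomatic item sits beside the VAS and is repeated at each visit, and 2.7 provides a chi-square test for qualitative variables. A reader might infer from 2.4.2 that resolved pain cannot be recorded at all. The documents do not support that, because a child whose pain resolves moves from symptomatic to asymptomatic. What remains is that the VAS, the score that enters means and t-tests, cannot clearly show resolution, and no rule links the two items.

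It can also be said that 1 was meant as the floor, including no pain. That is possible. If so, no pain and minimal pain share one value and the text should say so. Blank scores are likewise only one possible reading; the article does not say that fields will be left empty.

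On precision, the defence is right that enrolling pain-free children is a stated scope, that they can still worsen and so are informative, and that an analysis plan not shown may adjust for baseline. It is also right that most of the fall from 80% in the illustration reflects fewer symptomatic children, which no analysis recovers. Restriction to symptomatic children is not needed either, since adjustment in all children does about as well (51% and 34%).

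Finally, a reader might set one lost scale point against the 2-unit difference in 2.6. That section names no outcome, so the comparison has no basis.

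**Conclusion.** The point holds for the numeric score. As written, 2.4.2 has no value for no pain, in a trial that foresees pain-free children at entry and during follow-up. This follows from the text and needs no assumption.

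The loss of precision holds conditionally. It arises if VAS scores are compared in all children without adjustment, which is what the tests named in 2.7 would do if applied directly to final scores. On the assumed values, pooling costs about 22 percentage points of power if half the children have pain and about 16 if 30% do, and slightly less with the treated-arm variance corrected. The true size cannot be derived because the symptomatic share is not given. It would be tempting to conclude that the pain comparison loses most of its power through pooling; the split in the working does not bear that out.

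Pain is not declared primary, so an effect on the trial's main conclusion is not established. The change is worth making because the symptom half of the objective depends on this score and the correction is nearly free.

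**What to change.** - In 2.4.2 and on the Appendix C form, define the VAS as 0 to 10 with 0 = no pain and 10 = maximum pain. State that every child is scored at every visit, including children recorded as asymptomatic.
- In 2.7, state that pain is compared between arms in all children, adjusting for baseline VAS and baseline symptomatic status.
- Add the comparison in children symptomatic at baseline as a supporting analysis.
- Report new-onset pain by arm in children asymptomatic at baseline.

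The cost is one line in 2.4.2, one field on the form and slightly more analysis. The supporting analysis rests on fewer children, but the main pain comparison keeps everyone.
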